#### Study groups

##### Usual care (waitlist control) group

Participants allocated to the waitlist control group will receive standard diabetes care from their usual provider. In New Zealand, these clinics are attended regularly (usually a minimum of every 3 months) to provide diabetes care by a multi-disciplinary team (i.e., paediatric or adult endocrinologist/diabetologist (depending on patient age), diabetes nurse specialist, dietician, psychologist/social worker). Participants will continue self-monitoring their blood glucose levels with their usual glucose meter per recommendations from their clinical care team. All other aspects of diabetes care will remain with their usual clinical care facility and will be in no way altered by the study team. No additional diabetes care, support, or advice will be provided by the study team making the provision of the FreeStyle Libre (Abbot Diabetes Care, Witney, Oxon, UK) FGM system, along with instruction in its use, the only difference between intervention groups. To maximise study retention in the control group, participants allocated to this group will receive FGM for 6-months at the completion of their 6-month follow-up study visit.

##### Flash glucose monitoring (intervention) group

Participants randomized to the intervention group will continue routine care (as described above) and receive a FGM system, which includes a reader, USB cable, power adapter, user’s manual, and quick start guide. In addition, the FGM group will be provided and talked through a 1-page single-sided handout summarising key educational information from the manufacturer’s user manual, instructions to confirm their blood glucose level before therapeutic interventions or corrective action if hypoglycaemic or hyperglycaemic glucose levels or symptoms occur, recommendations to prolong sensor life, and instructions to report adverse events (see Supplementary material). The first FreeStyle Libre sensor will be applied by trained staff (i.e. diabetes nurse or research staff trained by a FreeStyle Libre distributor territory manager) at the baseline visit using the manufacturer’s quick start guide. Participants will receive a spare sensor in case of sensor failure before the follow-up visit and a “patch” made from pre-cut kinesiology tape (FreeStyle Libre patch, Rockadex, Perth, Australia) to apply over the sensor in the event the sensor is at risk of falling off prematurely (i.e., due to impaired adhesion to skin or sensor adhesion to the adhesive applied to the skin). An alternative product (Hypafix®, BSN medical GmbH, Hamburg, Germany) will be provided to participants with a known skin sensitivity to Rockadex.

Participants will return in 14 days for the sensor site to be inspected for skin problems, apply the next sensor under supervision, and receive a 3-month FGM supply (i.e., 6 sensors and Rockadex or Hypafix patches). At this 14-day follow-up visit, staff will briefly provide more advanced FGM education on the trend arrows (specifically, the rate of change associated with each arrow direction and arrows indicating the need for a blood glucose check), the target glucose range graph, and instructions to review glucose readings on a computer using a 2-page handout (see Supplementary material). In exceptional circumstances, such as participants living more than 3 h from a clinic, the participant will apply their first sensor under trained staff supervision, receive a 3-month sensor supply, and will be followed-up in 14-days via teleconference software (Zoom, Zoom Video Communications, San Jose, CA, USA). Participants will apply their sensor unsupervised every 2 weeks for the remainder of the study. No further FGM education will be provided and no adjustments to treatment will be made by study staff. Furthermore, study staff will not interfere with participants’ adherence to flash glucose monitoring. Participants will be instructed to seek guidance on scanning frequency from their lead diabetes care provider.

Additional FGM supplies will be provided at the 3-, 6-, and 9-month follow-up visits. During all follow-up visits, retrospective glucose readings will be downloaded from the FGM reader for the previous 2 weeks, and reviewed for glucose levels below 4.0 mmol/mol between the hours of 10 pm and 7 am. All events of nocturnal hypoglycaemia in the previous 2 weeks will be reported to the appropriate diabetes care provider for follow-up.

### Procedures

The baseline measurements will be collected approximately 7 days from the screening visit. Follow-up assessment visits will be scheduled within a 14-day window, defined as 7 days before and 7 days after the due date. Assessment visits will be undertaken by data collectors trained centrally on the study requirements and measurement procedures. Blinding participants and research staff to group allocation will not be feasible. Participants will receive a $20 gift voucher in recognition of participation at each of the baseline and follow-up assessment visits.

### Outcome measures

The primary outcome measure is the difference in change in HbA1c between groups at 6-months.

All other measures are for secondary and tertiary (exploratory) outcomes. The timing of all assessments is presented in Table 2.

**Table 2 Tab2:** Managing Diabetes in a ‘Flash’ schedule of assessments

	Time point				
Outcome	Baseline	3 m	6 m	9 m^a^	12 m^a^
Adverse events					
Cutaneous, diabetic ketoacidosis, severe hypoglycaemia	Every 2 weeks from baseline				
Device performance					
FGM/SMBG device malfunctions, FGM sensor failures	Every 2 weeks from baseline				
Clinical					
Glycaemic control	X	X	X	X	X
Height	X	X	X	X	X
Weight	X	X	X	X	X
Glucose monitoring behaviour					
Blood glucose monitoring	X	X	X	X	X
Interstitial glucose monitoring		X	X	X	X
Habitual sleep and physical activity					
Sleep	X	X	X		
Physical activity	X	X	X		
Participant reported					
Diabetes treatment satisfaction	X	X	X		X
Fear of hypoglycaemia	X	X	X		X
Flash glucose monitoring acceptability		X	X		X
Health-related quality of life (generic)	X	X	X		X
Health-related quality of life (diabetes-specific)	X	X	X		X
Sleep quality and quantity	X	X	X		X

^a^ Denotes continuation phase of study

Abbreviations: *FGM* Flash glucose monitoring, *SMBG* self-monitoring blood glucose

### Adverse events and glucose monitoring device performance

All participants will be sent a link to an electronic questionnaire fortnightly, via both text and email, to report any episodes of cutaneous problems (e.g., infection, itching, rash, pain, subcutaneous haemorrhage), severe hypoglycaemia (i.e., child experiences altered mental status and as a result is unable to assist in their care, or is semiconscious or unconscious) [41], diabetic ketoacidosis (DKA), or missing school/work due to their diabetes. Up to four contact attempts will be made to non-responders. Data from safety surveys will be reviewed by research staff upon receipt by the study team. Participants will be referred to their general practitioner, diabetes team, or emergency department, as appropriate, for management of medical events. Adverse events (events which result in harm to a participant) will be reported to an internal safety monitoring committee made up of co-investigators with a clinical background and expertise in trials and diabetes.

The adverse events questionnaire will also collect data on FGM performance (i.e., sensor problems, reader problems), FGM adherence (i.e., duration of time each sensor is worn) and blood glucose meter performance (i.e., device malfunctions).

### Clinical outcomes

#### Anthropometry

Trained staff members will measure adolescents’ weight and height using standard procedures and calibrated instruments. Weight will be measured once with a fixed scale (DigiTol, Toledo, Switzerland or similar) or portable scale (Tanita Corporation, Japan or similar) to the nearest 0.1 kg, with shoes and heavy clothing removed. Height will be measured once to the nearest 0.1 cm using a fixed stadiometer (Harpenden stadiometer, Holtain Limited, Pembs, UK or similar) or a portable stadiometer (Leicester Height Measure, Invicta Plastics Ltd., Oadby, England). Portable devices will be used when measurements are conducted outside the clinic (participants’ home or a community centre). Height and weight will be used to calculate body mass index (BMI)- z-scores using Centers for Disease Control and Prevention growth standards [42].

#### Demographics

At the screening visit, a self-administered questionnaire will collect demographic information including age, gender ethnicity, address, and education level. Participants may choose to select more than one ethnicity; however, each person will be allocated to a single ethnic group for the purposes of statistical analyses that will be prioritised in the order of Māori, Pacific, Asian and European/Other [43]. The address where the participant lives more than 50% of the time will be used to assess their NZDep2013 deprivation score, which is a validated index of the relative socioeconomic deprivation of the area in which an individual lives [44].

#### Glycaemic control

Glycated haemoglobin (HbA1c) will be measured by traditionally calibrated point-of-care instruments (DCA Vantage Analyzer, Siemens Healthcare Diagnostics, Ireland), which meets acceptance criteria for HbA1c [45]. Measurements > 130 mmol/mol (maximum reading possible) will be recorded as 130.

#### Glucose monitoring behaviour

##### Self-monitoring blood glucose

The mean blood glucose level and total number of blood glucose tests will be downloaded into SmartLog (SmartLog Diabetes Management Software version 2.4.4, i-SENS, Inc., Seoul, Korea) from the currently funded blood glucose meter (CareSENS dual, i-SENS, Inc., Seoul, Korea) for the previous 2 weeks and recorded. Insulin pump data (if participant using a pump) will be downloaded using diasend® (Diasend/Glooko, Goteborg, Sweden) for the previous 2 weeks, and the mean blood glucose level and the mean number of tests recorded.

#### Flash glucose monitoring

All data will be downloaded at every follow-up visit and exported from the FGM reader using the FreeStyle Libre computer software version 1.0 (Abbott Diabetes Care, Ltd., Witney, Oxon, UK). Individual glucose measures, mean interstitial glucose level, and frequency of scans in the previous two weeks will be recorded.

#### Health status and quality of life

Validated instruments will assess the self-reported impact of FGM on adolescents’ health and quality of life at baseline, 3-, 6-, and 12-months. These instruments have been widely used in research and have demonstrated reliability and validity in this population. Data will be collected via electronic (REDCap; Research Electronic Data Capture) self-administered questionnaires or paper questionnaires prior to clinical assessments and the order of administration will be standardized to increase reliability. REDCap [46] is a secure, web-based application designed to support data capture for research studies. Together the questionnaires will take between 30 and 45 min to complete. All questionnaires are administered in English. Participant reported outcomes including overall health-related generic quality of life, health-related diabetes-specific quality of life, fear of hypoglycaemia, diabetes treatment satisfaction, and sleep outcomes will be monitored during the study and clinical care teams will be notified if participants report physical or mental problems necessitating follow-up.PedsQL™ generic core scale

The Paediatric Quality of Life Inventory (PedsQL™ 4.0) Generic Core Scale [47] is a 23-item measure of four dimensions related to an adolescents’ health-related quality of life (physical functioning, emotional functioning, social functioning, school functioning) in the past month. Scores are reported on a scale from 0 to 100 with higher scores indicating better health-related quality of life. Internal consistency reliability has been shown to be acceptable for the Total Scale Score (alpha = 0.88), Physical Health Summary Score (alpha = 0.80), and Psychosocial Health Summary Score (alpha = 0.83). [48] The PedsQL™ 4.0 has been shown to distinguish between children and adolescents with diabetes and children and adolescents without diabetes [49].2.PedsQL™ diabetes module

The Paediatric Quality of Life Inventory Diabetes Module for Type 1 diabetes (PedsQL™ Version 3.0 Type 1 Diabetes module) [49] is a 28-item self-report measure of T1D specific health-related quality of life in adolescents in the past month. The scoring is identical to the PedsQL 4.0, with higher scores indicating fewer symptoms or problems. In a sample of children and adolescents with T1D and type 2 diabetes, the mean alpha-coefficient for the Diabetes Module scales was acceptable (alpha = 0.71, range: alpha = 0.63 to 0.81) and the Diabetes Module demonstrated inter-correlations with dimension of generic and diabetes-specific HRQOL [49].3.Fear of hypoglycaemia

Participants aged 18–20 years, inclusive, will complete the adult Hypoglycaemia Fear Survey-II (HFS-II) [50, 51], which is a 33-item measure of fear of hypoglycaemia (behaviour subscale) and worries related to various aspects of hypoglycaemia (worry subscale) in the past 6 months. All items are summed to obtain a Total Score (score range: 0–132; higher Total Scores reflect a greater fear of hypoglycaemia) and each set of items for the two subscales are summed to yield a Behaviour Score (score range: 0–60; a higher score reflects a greater tendency to avoid hypoglycaemia and/or its negative consequences) and a Worry Score (range score: 0–72; a higher score indicates more worry concerning episodes of hypoglycaemia and its consequences). These sums will be divided by the total number of items in each scale/subscale to obtain an item mean score. The Hypoglycaemia Fear Survey for Children (HFSC) [52] is a 25-item instrument adapted from the adult HFS. The HFSC will be completed by adolescents in the study aged 13–17 years, inclusive.

Overall, higher scores reflect greater fear of hypoglycaemia, a higher score on the Behaviour Subscale reflects a greater tendency to avoid hypoglycaemia and/or its negative consequences, and a higher score on the Worry Subscale indicates more worry concerning episodes of hypoglycaemia and its consequences. The CHFS has shown adequate internal consistency (HFSC behaviour subscale alpha = 0.70; CHFS worry subscale alpha = 0.89; and CHFS-Total alpha = 0.85) [52]. HFSC worry subscale and total scores have been shown to correlate significantly with other measures of anxiety. [52] HFS-II and CHFS total scores and subscale scores will be calculated as z-scores standardised to the instrument-specific and baseline means and standard deviations.4.Diabetes treatment satisfaction

The Diabetes Treatment Satisfaction Questionnaire- status version (DTSQs) [53] is a 12-item measure of a patient’s current treatment satisfaction that includes subscales to measure diabetes treatment satisfaction and perceived diabetes control. The Diabetes Treatment Satisfaction Questionnaire-change version (DTSQc) is a 12-item self-report measure of change in a patient’s satisfaction with their diabetes treatment regimen, which was developed to overcome potential ceiling effects (i.e., where respondents score maximum or near-maximum satisfaction at baseline and can show little or no improvement at follow-up).

#### Flash glucose monitoring acceptability

Adolescents in the FGM group will evaluate the FreeStyle Libre FGM system acceptability at 3- and 6-months, and all participants will answer acceptability questions at 12-months using a non-validated instrument adapted from previous similar research [25]. On an ordinal scale from 0 (strongly disagree) to 5 (strongly agree), participants will rate their opinion in regards to the following areas: acceptability of sensor application, wear/use of the device and comparison to SMBG.

#### Sleep and physical activity

##### Accelerometry

Adolescents will wear an accelerometer (ActiGraph, wGT3X-BT, Pensacola, FL, USA) on the non-dominant wrist for 7 days and 8 nights (continuously), except during activities involving water (e.g., showering and swimming) prior to the baseline and 3- and 6-month follow-up visits. The ActiGraph wGTX3- BBT is a motion sensor worn like a wrist-watch that gives objective information about physical activity and sleep, including sleep disturbance. ActiGraphs will be initialized using 15 s epochs. Data will be scored using the count-scaled algorithm developed within our lab for scoring sleep and physical activity in MATLAB (MathWorks, Natick, MA, USA) [54, 55]. Standard sleep variables from the actigraphy outputs will be calculated [56]: sleep onset, sleep offset; sleep duration (sleep period time and total sleep time); wake after sleep onset; and sleep efficiency. Given the lack of validated cut-offs for determining intensity of activity spanning adolescents and young adults, activity accelerometry will be measured as counts per minute. The data will enable an exploratory analysis to investigate the association between wearing the FreeStyle Libre and changes in activity.

##### Pittsburgh sleep quality index

Habitual sleep will be measured at baseline, 3- and 6-months using the Pittsburgh Sleep Quality Index (PSQI) [57]. The PSQI is a 19-item self-report measure of subjective sleep quality and sleep quantity in the previous month. Originally devised as a 19-item questionnaire for adults, five questions related to sleeping with a bed partner will not be included. The PSQI generates 7 domains for subjective sleep quality, sleep latency, sleep duration, sleep efficiency, sleep disturbance, sleep medication, and daytime dysfunction, with each component score ranging from 0 to 3, and summed to produce a global score. A global score > 5 suggests a “poor sleeper” with significant sleep complaints. There is evidence of acceptable internal consistency (alpha = 0.77) with item-rest correlations ranging from 0.43 to 0.61 in adolescents [58].

#### Other measures

##### Parent/caregiver self-reported questionnaires

At baseline, parents of enrolled participants who provide written consent for their own participation in the study will complete a short questionnaire collecting demographic characteristics (e.g., age, gender, education level, and ethnicity). At baseline, 3-, 6-, and 12-months post-baseline, parents’ perceptions of their child’s wellbeing will be assessed by a self-report questionnaire. Parents/caregivers will also complete parent-proxy versions of questionnaires to assess their perceptions of their child’s quality of life [47, 49], their own fear of their child experiencing hypoglycaemia [52], and their own satisfaction with their child’s diabetes treatment [53]. The DTSQ and HFS are not available for parents of participants 18 years of age and older.

### Data management

All study participants will be assigned a non-informative study identification number. Data will be recorded and stored electronically in REDCap, which is hosted at the University of Otago. REDCap features will help ensure adherence to time-frames, compliance to measurement procedures, and completeness of data. Data will be routinely checked for missing and/or erroneous values by the study coordinator. Only research staff and investigators will have access to the electronic study records. The ethics committee did not require auditing for this study.

At the end of the study, original data collection sheets and written informed consent will be stored securely at the lead site along with copies of all data collected electronically. At the end of the study, the lead investigator will retain an electronic copy of the cleaned data set, with all identifying information removed.

### Statistical analysis

Means and standard deviations (SDs) will be reported for continuous variables (i.e., age, diabetes duration, HbA1c, glucose monitoring behaviour, questionnaire scores) that are approximately normally distributed, geometric means and SDs for those that are approximately log-normally distributed, and medians and IQRs otherwise. Categorical variables will be described as the number and percent of participants in each category (i.e., gender, ethnic group, insulin regimen). Adverse events will be categorised by the type of event (e.g., severe hypoglycaemia, DKA, sensor insertion issues, sensor wear issues). The frequency of events will be reported by event category.

A mixed linear model will be used to test the difference in HbA1c, with the primary outcome being at 6-months, between the intervention and control groups, using data from all time points with a random participant effect used to accommodate the repeated measures and a group-time interaction to model differences in longitudinal changes. Changes in number of glucose measurements performed and patient-reported outcome measures (i.e., PedsQL generic core scale, PedsQL diabetes module, HFS, and DTSQs scores) from baseline through to 6 months will be calculated by comparing scores from control and intervention group participants using Poisson (or negative binomial regression if there is evidence of over-dispersion) for count outcomes and linear mixed models for continuous outcomes with all collected data included. Model residuals will be examined along with the distribution of random effects. If residuals are positively skewed, natural logarithmic transformations will be investigated and retained if these improve the satisfaction of model assumptions. Mixed quantile regression will be investigated for continuous outcomes if issues with model residuals remain following such transformations. If HbA1c values of 130 are observed, mixed Tobit models with right censoring at 130 will be used for this outcome instead. All mixed models will use restricted maximum likelihood (REML) estimation for the variance components.

Some secondary analyses, such as those involving the wait-list control after they cross over, will only include participants from one group and so group (and group-time interaction) terms will not be included in these models.

The main analyses will follow a modified intention- to-treat principle with all participants analysed in the group to which they were randomised, regardless of actual sensor wear. Per protocol analyses will be also be investigated by including only those from the FGM group who scanned at least 12 out of 14 days in the two weeks prior to the 6-month study visit and excluding any participants from the SMBG group who used FGM at any time during the study. All models will include variables used in minimization [59].

Any missing HbA1c values will be imputed using multiple imputation with chained eqs. (100 imputations after at least 100 burn-ins) and with the imputation model including: gender, HbA1c status at baseline as well as values of that variable from other time points, insulin regimen, frequency of self-monitored glucose (capillary or interstitial) and socioeconomic status. If missing data exceeds 10%, plausible scenarios involving informative missing data will be investigated to explore the robustness of findings.

Statistical analyses will be performed using R 3.5.2 or Stata 15.1 software (or later versions) with two-sided *p* < 0.05 considered significant. To maintain the integrity of the study, statistical analyses will be performed by the biostatistician blinded to group allocation.

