• Planned to continue with routine clinical care during the initial 6-month RCT	• Currently using a CGM or FGM device or has used one continuously (other than for intermittent hospital use) within the previous 4 months
• Resident in and expecting to remain in regions affiliated with the Canterbury, Capital and Coast, and Southern District Health Boards for the following year	• Participation in another device or drug study that could affect glucose measurements during the study period
	• Pregnant, lactating, or plan to become pregnant
• Ability to understand study procedures, including English language proficiency, and to comply with them for the entire length of the study	
	• Inability of individual (for those aged 16 years and older) or legal guardian (for those aged 13–15 years) to give written informed consent

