### Sample size

Based on our data from an earlier study in this population, the standard deviation of HbA1c amongst those with values 75 mmol/mol (≥9%) or greater (and irrespective of self-monitoring blood glucose frequency) was 18.6 mmol/mol [38, 39]. Assuming a correlation between repeated measures of 0.7, a sample size of 58 (29 per group) would provide 80% power to detect a difference in mean changes for HbA1c of 1% (10.93 mmol/mol) using a two-sided test at the 0.05 level. This would be considered a clinically important difference, of a similar magnitude to other proven technologies such as insulin pumps or CGM [40]. To account for a small amount of missing data and loss to follow-up (anticipated to be < 10%), we will recruit a sample size of 64 (32 participants per group) at baseline. Reasons for non-retention of participants (i.e., consent withdrawn, moving outside of the study DHBs, or lost to follow-up) will be recorded and shown in a CONSORT flow diagram (Fig. 1).

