### Study procedures

#### Screening and enrolment

After being given an opportunity to review the participant information sheet and consider whether they want to be involved in the study, and prior to screening, adolescents and young adults aged 16–20 years and a parent/guardian of adolescents aged 13–15 years must provide written informed consent for their participation in the study. Parents/guardians will also be asked for their consent to provide information about themselves. Adolescents aged 13–15 years must also provide written assent for their participation. A point of care (POC; DCA Vantage Analyzer, Siemens Healthcare Diagnostics, Ireland) HbA1c will be measured when POC HbA1c has not been assessed in the previous 14 days. All female patients will provide a urine sample and study staff will follow the manufacturer’s guidelines for conducting the pregnancy test (EasyCheck® Pregnancy Test, Hangzhou Clongene Biotech Co, Ltd., China). Date of diabetes diagnosis (for subsequent calculation of duration of diabetes), current insulin regimen, insulin dosing, HbA1c measurements in previous 6 months, and co-morbidities will be recorded from electronic medical records. Diabetic ketoacidosis in the past 6 months, and severe hypoglycaemia events (defined as requiring the assistance of another person to treat [41]) in the past 6 months will also be recorded from electronic medical records to provide baseline estimates of frequency for these events. Any patient can withdraw (or be withdrawn by their parent or guardian for those aged 13–15) from the study at any point and return to their usual medical care.

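### The exploratory per-protocol rule removes controls who used FGM but keeps those who used CGM, and its time window, read literally, also covers the planned crossover

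*Protocol article*

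**What the plan says.** Two places in the protocol article define the per-protocol set: the tertiary objectives under Aim, objectives and hypotheses, and Statistical analysis. Both keep FGM-arm participants who scanned on at least 12 of the 14 days before the 6-month visit. For the control arm, both apply the same rule: "excluding any participants from the SMBG group who used FGM at any time during the study".

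The entry rule is wider. Among the exclusions in Table 1 (Recruitment) is: "Currently using a CGM or FGM device or has used one continuously (other than for intermittent hospital use) within the previous 4 months".

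The Background section on flash glucose monitoring describes CGM as a related but distinct technology, which differs from FGM in price, calibration and alerts. In Sample size, the 1% target is described as "of a similar magnitude to other proven technologies such as insulin pumps or CGM".

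On timing, Study design sets a total study period of 12 months for each participant. That section and the section on the usual care group say that controls receive FGM for the second 6 months.

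**The concern.** A per-protocol comparison of FGM with SMBG is meant to set FGM users against people monitoring by finger prick alone. The rule does this for one kind of sensor only. A control who obtains FGM outside the study is removed, while a control who obtains CGM is kept as a clean SMBG user. The article itself expects CGM to lower HbA1c by about as much as the trial hopes FGM will. Such a control lowers the mean of the comparison group and shrinks the estimated difference.

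The second problem is the window. The control-arm rule has no end point other than the end of the study, yet controls are due to use FGM from month 6. If the rule is programmed as written, the per-protocol control group is left only with those who declined or never reached the crossover.

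What is at stake is how the exploratory per-protocol results can be read. The main result is not at stake.

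**Working it through.** **Step 1. Entry rule against post-entry rule.**

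| Place in the protocol article | FGM | CGM |
|---|---|---|
| Table 1, exclusion at entry | excluded | excluded |
| Tertiary objectives, control arm | excluded | not mentioned |
| Statistical analysis, control arm | excluded | not mentioned |
| Both places, FGM arm | scanning criterion only | not mentioned |

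Because the Background separates CGM from FGM, and Table 1 names both, the term FGM in the per-protocol rule cannot be read as covering CGM. In the FGM arm, someone who had moved wholly to CGM by month 6 would probably fail the scanning criterion. Someone who used CGM earlier and then returned to scanning would pass it.

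**Step 2. The window.** The study period is 12 months (Study design). Controls receive FGM at the end of their 6-month visit (Usual care group). A control who takes it up has then used FGM during the study, so the literal rule excludes that person. The primary and secondary analyses that the per-protocol analysis repeats concern the 6-month trial period, so nothing in the objectives calls for a window beyond month 6.

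**Step 3. The plan's own figure.** Inputs from Sample size: SD 18.6 mmol/mol, correlation 0.7, target difference 10.93 mmol/mol, power 80%, "using a two-sided test at the 0.05 level".

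- SD of change = 18.6 × √(2 × (1 − 0.7)) = 14.41 mmol/mol.
- n per group by the normal approximation = 2 × (1.960 + 0.842)² × 14.41² / 10.93² = 27.3, rounded up to 28.
- With the noncentral t distribution, power is 0.796 at 28 and 0.810 at 29 per group. The stated 29 per group (58 in total) is reproduced.

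**Step 4. What one missed control could do (illustration only).** Assume that one control starts CGM and gains the full target effect by month 6. With m controls analysed, the control mean falls by 10.93 / m.

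- m = 29 (planned number analysed): 10.93 / 29 = 0.377, about 0.38 mmol/mol, or 1/29 = 3.4% of the target.
- m = 32 (all recruited controls): 10.93 / 32 = 0.34 mmol/mol.
- Half the assumed effect with m = 29: 0.5 × 10.93 / 29 = 0.19 mmol/mol.

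The shift grows in proportion to the number of such controls. The article gives no figure for that number, so the calculation stops here.

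**The case against.** The strongest reply is that this touches only an exploratory analysis. The per-protocol analysis is a tertiary objective, the article already warns that it may be confounded by who complies, and the main analysis keeps everyone in the randomised group. That is correct, and it limits the reach of the point.

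A second reply is that few controls may start CGM. The article says CGM costs more than FGM, that FGM is not publicly funded in New Zealand, and that controls are promised FGM at 6 months. This also stands, and it is a reason to put no overall size on the effect. It does not explain why a rule that bothers to exclude FGM should leave CGM out.

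A third reply is that the authors plainly meant the 6-month comparison when they wrote of the study. That is probably the intention, but the wording does not say so, and the article elsewhere defines the study as 12 months.

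A reader might go further in two ways that the article does not support:

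- One might infer that CGM or pump starts distort the primary contrast. The primary comparison is FGM added to usual care against usual care, analysed as randomised. Changes in other care are part of that contrast, and similar uptake in both arms does not bias it.
- One might infer that pump and insulin-regimen changes go unseen because regimen is described as recorded at screening. However, pump data are downloaded as part of blood glucose monitoring, which Table 2 schedules at baseline and at every follow-up visit. Table 2 also omits items, such as demographics and insulin regimen, that other sections say are collected. In a condensed article, absence from that table is weak evidence that something is not recorded.

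**Conclusion.** The point holds for the per-protocol definition and no further. The control-arm rule omits CGM, which the same article bars at entry and credits with an effect close to the target. Its time window, taken literally, removes every control who takes up the planned crossover.

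The direction of the first fault is towards zero, provided that CGM lowers HbA1c in controls as the sample-size section implies. Its size is unknown. The figure of 0.38 mmol/mol per control assumes the full 10.93 mmol/mol effect and 29 controls analysed, and it is not a forecast. The second fault follows from the wording alone and needs no assumption beyond controls taking up the FGM they are offered.

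The primary analysis and the sample size need no change on this account.

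**What to change.** In the tertiary objectives and in Statistical analysis, replace the control-arm criterion with: exclude SMBG participants who used any FGM or CGM between baseline and the 6-month visit. Add for the other arm: exclude FGM participants who used CGM in the same period.

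So that the rule can be applied, ask participants in both arms about CGM use at the 3- and 6-month visits, unless the full protocol already provides for this. The items that the article describes (FGM reader download, meter and pump downloads, and the fortnightly questions on FGM and meter performance) do not name CGM.

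The cost is a reworded criterion in two places and one question at two visits that already take place. The exploratory per-protocol set may lose a few participants.
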